**BUDGETARY REQUIREMENT:**

| Details of items with quantity | Study period (6 Months) | Total (Rs) |
| --- | --- | --- |
| Manpower | 1 SRF (Senior Resident, Department of Pharmacology)  1 JRF (Junior Resident, Department of General Medicine) | Nil since he/she is part of institute resident-ship |
| Study drugs | Available in the institute |  |
| Equipment | Available in the institute |  |
| Investigations: n= any till end of the study  ECG (Baseline, every 72 hours)  LFT (Baseline and every 72 hours)  KFT (Baseline and every 72 hours)  CBC (Baseline and every 72 hours)  Others specific marker of an organ involvement | Available in the institute |  |
| Chemicals/ Reagents/ Consumables | Available in the institute |  |
| Contingencies | NA |  |
| Total |  |  |

Note: -

1. All expenditure should be logically justified by the proposed project
2. All purchases will be made as per GFR and institutional financial guidelines for research projects.

**Country ____________State___________________District_____________________Lane_________________**

**CLINICAL INCLUSION CRITERIA**

| One or more of these during this illness | A history of self-reported feverishness or documented fever | ☐Yes ☐No |
| --- | --- | --- |
|  | Cough | ☐Yes ☐No |
|  | Dyspnoea (shortness of breath) OR Tachypnoea | ☐Yes ☐No |
|  | Clinical suspicion of ARI despite not meeting criteria above | ☐Yes ☐No |

**DEMOGRAPHICS**

| Sex at Birth ☐Male ☐Female ☐Not specified Date of birth: [__][__]/[__][__]/[__][__][__][__]  If date of birth is unknown, record: Age [___][___][___]years  Healthcare Worker? ☐Yes ☐No ☐Unknown  Laboratory Worker? ☐Yes ☐No ☐Unknown  Pregnant? ☐Yes ☐No ☐Unknown ☐N/A If yes: Gestational weeks assessment [___][___] weeks |
| --- |

**CO-MORBIDITIES (existing prior to admission) (Unk = Unknown)**

| Chronic cardiac disease (not hypertension)  Yes ☐No ☐Unk | Diabetes ☐Yes ☐No ☐Unk |
| --- | --- |
| Hypertension Yes ☐No ☐Unk | Current smoking ☐Yes ☐No ☐Unk |
| Chronic pulmonary disease ☐Yes ☐No ☐Unk | Tuberculosis ☐Yes ☐No ☐Unk |
| Asthma Yes ☐No ☐Unk | Asplenia Y☐es ☐No ☐Unk |
| Chronic kidney disease ☐Yes ☐No ☐Unk | Malignant neoplasm ☐Yes ☐No ☐Unk |
| Chronic liver disease ☐Yes ☐No ☐Unk | Other ☐Yes ☐No ☐Unk  If yes, specify: ------------------------------------------------------------------------------------------------------ |
| HIV ☐Yes-on ART ☐Yes-not on ART ☐No ☐Unknown |  |

**MEDICATION Is the patient CURRENTLY receiving any of the following?**

| 1. Oral/orogastric fluids? ☐Yes ☐No ☐Unknown Intravenous fluids? ☐Yes ☐No Unknown 2. Antiviral? ☐Yes ☐No Unknown If yes: ☐Ribavirin ☐Lopinavir/Ritonavir ☐Neuraminidase inhibitor ☐Interferon alpha Interferon beta Other, specify: _________________________ 3. Corticosteroid? ☐Yes ☐No ☐Unknown If yes, route: ☐Oral ☐Intravenous Inhaled If yes, provide agent and maximum daily dose:____________ 4. Antibiotic? ☐Yes ☐No Unknown If yes, specify: ____________________ 5. Antifungal agent? ☐Yes ☐No Unknown, If yes, specify: ____________________ 6. Antimalarial agent? ☐Yes ☐No ☐Unknown If yes, specify____________________ 7. Experimental agent? ☐Yes ☐No ☐Unknown If yes, specify____________________ 8. Non-steroidal anti-inflammatory (NSAID) ☐Yes ☐No ☐Unknown 9. Angiotensin converting enzyme inhibitors (ACE inhibitors) ☐Yes ☐No ☐Unknown Angiotensin II receptor blockers (ARBs) ☐Yes ☐No ☐Unknown |
| --- |

**SUPPORTIVE CARE**

**Is the patient CURRENTLY receiving any of the following?**

| 1. ICU or High Dependency Unit admission? ☐Yes ☐No ☐Unknown 2. Oxygen therapy? ☐Yes ☐No ☐Unknown   If yes, complete all below O2 flow: ☐1-5 L/min ☐6-10 L/min ☐11-15 L/min ☐>15 L/min ☐Unknown  Source of oxygen: ☐Piped ☐Cylinder ☐Concentrator ☐Unknown  Interface: ☐Nasal prongs ☐HF nasal cannula ☐Mask ☐Mask with reservoir ☐CPAP/NIV mask Unknown   1. Non-invasive ventilation? (e.g.BIPAP/CPAP) ☐Yes ☐No ☐N/A 2. Invasive ventilation (Any)? ☐Yes ☐No ☐Unknown 3. Inotropes/vasopressors? ☐Yes ☐No ☐Unknown 4. Extracorporeal (ECMO) support? ☐ 5. Prone position? ☐Yes ☐No ☐Unknown |
| --- |

**Case Summary:**

**Travel and Contact history (if significant)**

**Physical examination: (with consent and after adequate precautions)**

1. **Mental status –**
2. **General appearance –**
3. **Vitals: PR - , RR - , BP - , Temp - , SpO_2_ -**
4. **Skin –**

| SYSTEM | Inspections | Palpations | Percussions | Auscultations |
| --- | --- | --- | --- | --- |
| 1. Chest (respiratory system) |  |  |  |  |
| 1. Chest (cardiovascular) |  |  |  |  |
| 1. Abdomen |  |  |  |  |

1. **Genito-urinary-Rectal exam –**
2. **Musculoskeletal Assessment –**
3. **Neurological Assessment –**

**LABORATORY RESULTS ON ADMISSION (*record units if different from those listed)**

| Parameter | Value | Not done | Parameter | Value | Not done |
| --- | --- | --- | --- | --- | --- |
| Haemoglobin (g/L) |  |  | Urine R/M (significant if any) |  |  |
| WBC count (x109/L |  |  | Sodium (mEq/L |  |  |
| Haematocrit (%) |  |  | Potassium (mEq/L) |  |  |
| Platelets (x109/L) |  |  | Calcium(mg/dL) |  |  |
| APTT/PT/INR |  |  | Lactate (mg/dL) |  |  |
| Total bilirubin (mg/dL) |  |  | Procalcitonin (ng/mL) |  |  |
| Direct bilirubin (mg/dL) |  |  | CRP (mg/L) |  |  |
| Albumin (g/dl) |  |  | LDH (U/L) |  |  |
| Globulin (g/dl) |  |  | Creatine kinase (U/L) |  |  |
| SGOT/SGPT (U/L) |  |  | Troponin (ng/mL) |  |  |
| Urea (mg/dL) |  |  | ESR (mm/hr) |  |  |
| Creatinine (mg/dL) |  |  | D-dimer (mg/L) |  |  |
| RBS |  |  | HbA1C |  |  |
| Others |  |  |  |  |  |

**Non-severe Treatment arms (NS-group)**

**PARTICIPANT ID I___I I___I I___I I___I I___I -- I___I I___I I___I I___I Date of enrolment [__][__]/[__][__]/[__][__][__][__]**

**Day of Hospitalization: _______________ Date of follow-up: [__][__]/[__][__]/[__][__][__][__]**

**VITAL SIGNS:**

| Temperature: °C Heart rate: beats per min Respiratory rate: breaths/min  BP: mmHg Hydration Status: Sternal capillary refill time >2seconds ☐Yes ☐No GCS:  Oxygen saturation (SPO2): % on ☐ room air ☐oxygen therapy ☐Unknown |
| --- |

Standard Treatment for non-severe cases (ST_NS_):

1. Strict Isolation: ☐Yes ☐No ☐Unk
2. Standard Precautions (Hand hygiene, Cough Etiquette, Wear surgical mask): ☐Yes ☐No ☐Unk
3. Nutrition: ☐Enteral ☐Parenteral ☐Unk
4. Supportive Pharmacotherapy (Antipyretic, Antiallergic, Cough Suppressant if any with days and frequency)

- ______________________________________________
- _______________________________________________
- ______________________________________________

1. Treatment of Comorbid Diseases(to mention condition and treatment given)
2. Oseltamivir (for patient who are tested positive for H1N1)

- Total number of days received:
- Dosage and Frequency:

1. Treatment Group:

☐Treatment Arm: A (Standard Treatment-ST_NS_)

☐Treatment Arm: B (Hydroxychloroquine 400 mg twice on first day followed by 400 mg per oral daily for 10 days + Standard Treatment -ST_NS_) ^^[[2]](#endnote-1)^^

**CLINICAL FEATURES (Unk = Unknown)**

| - Cough and sputum production - Sore throat - Chest pain - Shortness of breath - Confusion | ☐Yes ☐No ☐Unk  ☐Yes ☐No ☐Unk  ☐Yes ☐No ☐Unk  ☐Yes ☐No ☐Unk  ☐Yes ☐No ☐Unk | - Seizures - Vomiting - Nausea - Diarrhoea - Conjunctivitis - Myalgia - Other, specify_______ | ☐Yes ☐No ☐Unk  ☐Yes ☐No ☐Unk  ☐Yes ☐No ☐Unk  ☐Yes ☐No ☐Unk  ☐Yes ☐No ☐Unk  ☐Yes ☐No ☐Unk  ☐Yes ☐No ☐Unk |
| --- | --- | --- | --- |

**LABORATORY RESULTS ON FOLLOW UP (*record units if different from those listed)**

| Parameter | Value | Not done | Parameter | Value | Not done |
| --- | --- | --- | --- | --- | --- |
| Haemoglobin (g/L) |  |  | Urine R/M (significant if any) |  |  |
| WBC count (x109/L |  |  | Sodium (mEq/L |  |  |
| Haematocrit (%) |  |  | Potassium (mEq/L) |  |  |
| Platelets (x109/L) |  |  | Calcium(mg/dL) |  |  |
| APTT/PT/INR |  |  | Lactate (mg/dL) |  |  |
| Total bilirubin (mg/dL) |  |  | Procalcitonin (ng/mL) |  |  |
| Direct bilirubin (mg/dL) |  |  | CRP (mg/L) |  |  |
| Albumin (g/dl) |  |  | LDH (U/L) |  |  |
| Globulin (g/dl) |  |  | Creatine kinase (U/L) |  |  |
| SGOT/SGPT (U/L) |  |  | Troponin (ng/mL) |  |  |
| Urea (mg/dL) |  |  | ESR (mm/hr) |  |  |
| Creatinine (mg/dL) |  |  | D-dimer (mg/L) |  |  |
| Others |  |  |  |  |  |

Influenza virus: ☐Positive ☐Negative ☐Not done If positive, type ______________

Coronavirus: ☐ Positive ☐Negative ☐ Not done If positive: ☐ MERS-CoV ☐SARS-CoV-2 ☐Other

Other respiratory pathogen: ☐Positive ☐ Negative ☐Not done If positive, specify:___________

Other pathogen of public health interest detected: If yes, specify: __________________________

Radiological Investigations (if performed):

1. Chest X Ray/CT Performed (report):
2. Ultrasonography:
3. Others

Previous Treatment Regime (If any-to specify group with duaration):

☐Non-Severe Treatment arms (NS-group): Treatment Arm-A: ___________________________

Outcomes:

1. Clinical recovery ☐Yes ☐No
2. Time to 2019-nCoV RT-PCR negative in upper respiratory tract specimen in days (if applicable):
3. Time to defervescence in hours (if applicable)
4. Serious adverse events (specify if any)
5. **Final Clinician’s Impression:**

1. [↑](#footnote-ref-1)
2. **Severe Treatment arms (S-group)**

   **PARTICIPANT ID** I___I I___I I___I I___I I___I -- I___I I___I I___I I___I **Date of enrolment** [__][__]/[__][__]/[__][__][__][__]

   **Day of Hospitalization: _______________ Date of follow-up:** [__][__]/[__][__]/[__][__][__][__]

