| (e) | Details of procedure and methodology proposed to be used (300 words) including description of the potential risks and benefits, exclusion and Inclusion criteria outcome measures, statistical analysis:  ***Patient population:*** *Covid-19 positive symptomatic cases either non-severe or severe category*  ***Intervention:*** *Two therapeutic interventions for non-severe category and three for severe category as described below*  ***Comparator:*** *Parallel arm design, compared among other interventional arm in same category*  ***Outcomes:*** *Clinical and laboratory improvements in 72 hours of treatment*  **Patient population-**  Patients diagnosed with SARS-CoV-2 infection after positive reverse-transcriptase–polymerase chain reaction (RT-PCR) assay.  **Inclusion criteria:**   1. Age ≥18 years at time of participation in the study 2. Laboratory (RT-PCR) confirmed infection with SARS-CoV-2 3. Symptomatic (severe or non-severe) Covid-19 disease 4. Willingness of study participant to accept randomization to any assigned treatment arm   **Exclusion criteria:**   1. Use of medications that are contraindicated with Lopinavir/Ritonavir, Hydroxychloroquine/Chloroquine, or Ribavirin and that cannot be replaced or stopped 2. Patient already on antiretroviral therapy with Lopinavir-Ritonavir based regimen or on Hydroxychloroquine/Chloroquine or on Ribavirin 3. Any known contraindication to test drugs such as retinopathy and QT prolongation 4. Known allergic reaction or inability to delivery oraly to Lopinavir-ritonavir, Hydroxychloroquine/ Chloroquine, Ribavarin 5. Pregnant or breastfeeding females 6. Receipt of any experimental treatment for 2019-nCoV (off-label, compassionate use, or trial related) within 30 days prior to participation in the present study or want to participate after enrolment   **Potential benefits:**   1. All those who participate in the trial will benefit from possible effective treatment for COVID-19 infection 2. The study will highlight the therapeutic options in management of the symptomatic patients of COVID-19 infection   **Potential risks:**  The present study will be conducted on symptomatic patients of COVID-19 attending AIIMS Rishikesh. The patients will be categorised based on severity and treatment will be allocated accordingly.  Adverse drug reactions, though not frequent may be associated with the treatment. Proper supportive management will be given to the patients at the institute.  **Methodology**:  **Flow Diagram**  Patients of COVID-19 infection - After confirmation by RT-PCR at AIIMS, Rishikesh  Screening for inclusion in trial Enrolment Excluded  ♦  Not meeting inclusion criteria  ♦  Declined to participate  ♦  Other reasons  Categorisation based on severity of patient  **SEVERE group**  **NON-SEVERE group**  Randomisation to treatment arm:  **A. Standard Treatment (ST-S)**  **B. Hydroxychloroquine + Ribavirin + ST-S**  **C. Lopinavir+ Ritonavir + Ribavirin + ST-S**  Randomisation to treatment arm:   1. **Standard Treatment (ST-NS)** 2. **Hydroxychloroquine + Ribavirin + ST-NS**  RandomisationAllocation Monitor progress of patient in 72 hours Follow-Up Patient improve- continue same treatment  Clinical evaluation- @72 hours  Improve - Continue same treatment  Progress – achieved end point and Shift to institute protocol for further treatment  Patient do not improve/ Signs of severe disease  Shift to **SEVERE group** treatment arms after randomization with new consent Analysis Analysis  **Total duration of observation**:  28 days from the time of enrolment into the study OR till patient is discharged or death whichever is longer  **Design:** Open label, Parallel arm design, stratified randomised controlled trial:  Patients will be screened for the study after diagnosis of COVID-19 infection by Microbiology team. Patients will be categorised as non-severe or severe based on predefined criteria. The patient will be enrolled in the study after a written informed consent. Since it is an exploratory trial as COVID-19 being a new disease, all patients who came under the purview of the inclusion criteria within the study period and who have consented for the study will be included. Clinical evaluations will be done by a separate investigator. Blinding will not be performed but dynamic randomization will be done. Patients will be followed up for a period of 28 days from the day of enrolment.  At the time of enrolment, demographic information will be collected from participants, and relevant data on their medical histories, comorbidities, and risk factors for severe COVID-19. It will be documented along with investigations including CBC, ECG, LFT, RFT, G6PD status.  The patients will be categorised as severe based on the following criteria:   - Confirmed pneumonia on chest imaging, SPo2 <93%, Pao_2_:Fio_2_ <300 mg Hg - Respiratory failure (need of mechanical ventilation) - Septic shock - Multiple (>2) organ dysfunction syndrome (MODS) - Liver disease (Child Pugh score ≥ C, AST>5 times upper limit) - Patients with known renal impairment (estimated glomerular filtration rate ≤30 mL/min/1.73 m2) or receiving continuous renal replacement therapy, haemodialysis, peritoneal dialysis - Other single organ failure (e.g. heart, pancreas, etc) if specific definition meets   Non-severe category includes mild and moderate disease severity category other than severe ones.  **Treatment Schedule**  **Non-severe Treatment arms (NS-group):**   \| **Treatment Arm** \| **Drug** \| \| --- \| --- \| \| A \| Standard Treatment (ST_NS_) \| \| B \| Hydroxychloroquine 400 mg twice on first day followed by 400 mg per oral daily for 10 days + Ribavirin (2.4 g orally as a loading dose followed by 1.2 g orally every 12 hours) for 10 days + Standard Treatment (ST_NS_) ^6^ \|   **Standard Treatment for non-severe cases (ST_NS_):**   1. Strict Isolation 2. Standard Precautions (Hand hygiene, Cough Etiquette, Wear surgical mask) 3. Hydration 4. Proper Nutrition 5. Supportive Pharmacotherapy (Antipyretic, Antiallergic, Cough Suppressant) 6. Treatment of Comorbid Diseases 7. Oseltamivir (75 mg BD) for patient who are tested positive for H1N1   If the patient improves clinically the same treatment will be continued. If the patient do-not improve or shows sign of severity (mentioned above) the patient will be shifted to the severity arm (S-group) of the clinical trial and again randomization will be done and enrolled after new consent only for severe group. However, if intervention falls on HCQ arm, then it will be taken as end point reached and shifted to institute treatment protocol for further management.  **Severe group Treatment arms (S-group):**   \| **Treatment Arm** \| **Drug** \| \| --- \| --- \| \| A \| Standard Treatment (ST_s_) \| \| B \| Hydroxychloroquine 400mg BD on day1 followed by 400 mg once daily + Ribavirin (2.4 g orally as a loading dose followed by 1.2 g orally every 12 hours) for 10 days + Standard Treatment (ST_s_) \| \| C \| Lopinavir(400mg) + Ritonavir (100mg) two tablets twice daily+ Ribavirin (2.4 g orally as a loading dose followed by 1.2 g orally every 12 hours) for 10 days + Standard Treatment (ST_s_)^6^ \|   **Standard Treatment for severe patients: (ST_s_)**   1. Strict Isolation 2. Standard Precautions (Hand hygiene, Cough Etiquette, Wear surgical mask) 3. Fluid Therapy 4. Supportive Pharmacotherapy (Antipyretic, Antiallergic, Cough Suppressant) 5. Oxygen supplementation (As required) 6. Invasive ventilation (As required) 7. Antibiotic agents for other associated infections (according to 2019 ATS/IDSA guidelines for non-ICU and ICU patients) 8. Vasopressor support 9. Renal-replacement therapy 10. Treatment of Comorbid Diseases 11. Oseltamivir (75 mg BD) for patient who are tested positive for H1N1   Patients will be assessed for clinical and laboratory improvements in 72 hours of treatment. In case the patient does not respond to the current treatment regimen the patient will be shifted to institute protocol for current practice of treatment.  **Timelines of investigations: Repeated at 72hrs interval**   \| Investigations \| Baseline \| Next 72hrs \| \| --- \| --- \| --- \| \| CBC \| **✔** \|  \| \| LFT \| **✔** \|  \| \| KFT \| **✔** \|  \| \| HBA1C and Blood sugar \| **✔** \|  \| \| RT-PCR for SARS-Cov-2 (until 24hrs apart twice negative) \| **✔** \|  \| \| PT/INR \| **✔** \|  \| \| Serum Electrolytes \| **✔** \|  \| \| ABG \| **✔** \|  \| \| Chest Xray \| **✔** \|  \| \| ECG \| **✔** \|  \| \| Other organ markers as per involvement \| **✔** \|  \|     **Dose Modifications:**  If any serious adverse event is recorded, the participant will be withdrawn from the trial and management will be done accordingly as per institute policy.  **Recording adverse events:**  All adverse events will be recorded in the medical records in the first instance. All adverse events will be recorded with clinical symptoms and accompanied with a simple, brief description of the event, including dates as appropriate. Each adverse event will be assessed for severity, causality, seriousness and expectedness and informed to IEC within 24hours.  **Discontinuation/withdrawal of participants:**  A participant may be withdrawn from trial treatment whenever continued participation is no longer in the participant’s best interests, but the reasons for doing so must be recorded.  Reasons for discontinuing treatment may include:   1. Unacceptable drug toxicity 2. Development of progressive disease 3. Patients withdrawing consent to further trial treatment   **Endpoints:**  **Primary endpoints:**   1. Time to Clinical recovery (TTCR)    - TTCR is defined as the time (in hours) from initiation of study treatment (active or placebo) until normalisation of fever, respiratory rate, and oxygen saturation, and alleviation of cough, sustained for at least 72 hours.    - Normalisation and alleviation criteria: 2. Fever - ≤36.9°C or -axilla, ≤37.2 °C oral 3. Respiratory rate - ≤24/minute on room air 4. Oxygen saturation - >94% on room air 5. Cough- mild or absent on a patient reported scale of severe, moderate, mild, absent 6. Time to SARS-CoV-2 RT-PCR negative in upper respiratory tract specimen 7. Time to laboratory recovery of each organ involvement   **Secondary Endpoints:**   1. All causes mortality 2. Frequency of respiratory progression  - Defined as SPO2≤ 94% on room air or PaO2/FiO2 <300mmHg and requirement for supplemental oxygen or more advanced ventilator support.  1. Time to defervescence (in those with fever at enrolment) 2. Frequency of requirement for supplemental oxygen or non-invasive ventilation 3. Frequency of requirement for mechanical ventilation 4. Frequency of serious adverse events as per AIDS table grade of severity   **Statistical analysis**:  All COVID-19 positive patients will be included in the study after informed consent. Since it is an exploratory trial as COVID-19 being a new disease, all patients who came under the purview of the inclusion criteria within the study period and who have consented for the study will be included. Data will be described as mean+ SD for most of the parameters. Comparisons of the descriptive variables of the two arms will be performed using the Wilcoxon rank sum test for continuous variables and the chi-square or Fisher’s exact test for categorical variables. Primary analysis will include all patients (Intention to treat) and sub-group populations (per-protocol).  **Ethical clearance:**  The present study deals with a new infectious disease which has no definite treatment. Current therapy is based on symptomatic treatment. The present study explores the possibilities of new drugs in SARS-CoV-2 infection. The study will be conducted after IEC approval. Written informed consent will be taken from all participants.  **Safety Outcomes**  Safety outcomes will be determined according to the division of AIDS table for grading severity of adult adverse events (<https://rsc.niaid.nih.gov/clinical-research-sites/daids-adverse-event-grading-tables>), with specific focus on the events of gastrointestinal tract, arrhythmias, myopathies. In case of serious ADRs including death, compensation will be given as per institute protocol. |

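### Time to clinical recovery, the first of three listed primary endpoints, cannot be derived as the protocol defines it from the case report form

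*Protocol*

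**What the plan says.** Protocol, item (e), Primary endpoints, lists three endpoints: TTCR, time to a negative RT-PCR, and time to laboratory recovery of each affected organ. For the first, "TTCR is defined as the time (in hours) from initiation of study treatment (active or placebo") to the point at which all four components are met, the last being "alleviation of cough, sustained for at least 72 hours". Two of the component criteria matter here:

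- "Cough- mild or absent on a patient reported scale of severe, moderate, mild, absent"
- "Fever - ≤36.9°C or -axilla, ≤37.2 °C oral"

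The CRF has a follow-up form for the non-severe group and another for the severe group. On the items that feed TTCR, the two forms match:

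- **Outcomes:** "Clinical recovery ☐Yes ☐No". The next lines of the same block ask for time to negative RT-PCR in days and time to defervescence in hours.
- **Clinical features:** "Cough and sputum production" is one item, answered yes, no or unknown.
- **Vital signs:** "Temperature: °C Heart rate: beats per min Respiratory rate: breaths/min", followed by SpO2 with a tick for room air or oxygen therapy. No temperature site is asked for.
- **Header:** date of enrolment, day of hospitalisation and date of follow-up, with no clock times.

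**The concern.** A time-to-event endpoint in hours needs a dated and timed origin, a dated and timed event, and the component readings that define the event. Here the protocol text and the form that should supply the data do not match. A secondary endpoint, time to defervescence, has an hours field, while the primary endpoint defined in hours has only a tick box.

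An analysis plan cannot repair this, because it cannot use data that were never collected. A patient-reported cough grade, a measurement site and an onset hour are hard to recover afterwards. The practical substitutes would be an undated judgement of recovery in an open-label trial, or a recovery rule built from whatever the form does hold. The second would be a different endpoint from the one in the protocol.

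**Working it through.** The plan states no figure to reproduce. The check sets each element of the TTCR definition against the two follow-up forms, then works out what the dated sheets can give.

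**Element by element**

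| Element of the definition | What both forms record | Sufficient? |
| --- | --- | --- |
| Start of study treatment, to the hour | Date of enrolment; no first-dose date or time on the pages shown | No |
| Hour at which all four criteria are met | Recovery yes/no on a dated sheet | No |
| Held for 72 hours | No field | No |
| Cough mild or absent (four levels) | Cough with sputum: yes/no/unknown | Only if the answer is no |
| Temperature limit by site | °C without site | Not above 36.9 and up to 37.2 °C |
| Respiratory rate | Recorded | Yes, with the room-air tick |
| SpO2 on room air | Recorded, with room air or oxygen | Yes |

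**Cough.** Two of the four levels (absent, mild) meet the criterion and two (moderate, severe) do not. The form splits the scale after absent, so a yes covers one qualifying level and two non-qualifying ones. A patient with residual mild cough is recovered under the protocol but is indistinguishable on the form from one who is not.

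**Temperature.** At or below 36.9 °C a reading is normal at either site, and above 37.2 °C it is abnormal at either site. In between (37.0, 37.1 and 37.2 °C to one decimal) it is normal if oral and abnormal if axillary.

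**Resolution of calendar dates.** If two dates are *d* days apart, the true elapsed time lies between 24(*d* − 1) and 24(*d* + 1) hours, so the error can approach 24 h in either direction.
- *d* = 3: between 48 and 96 h, so 72 hours is not assured.
- *d* = 4: between 72 and 120 h, the first gap that assures it.

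Even then, the sheets show status at the visits and not between them.

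**Delay from the sheet interval.** The CRF does not say how often a follow-up sheet is completed. Assume that recovery falls uniformly between consecutive sheets and is dated at the later one. The average delay is then half the interval:
- daily sheets: 24 / 2 = 12 h;
- sheets only at the 72-hour evaluations: 72 / 2 = 36 h.

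**The case against.** The best defence is that the form is not empty. Each sheet is dated, and respiratory rate, temperature and SpO2 sit on it. A patient with no cough, a temperature of 36.9 °C or less, and normal respiratory rate and room-air saturation on consecutive sheets has a derivable recovery date, interval-censored to the gap between sheets. This stands. A reader might infer that TTCR cannot be computed for any patient, and the documents do not support that. What is lost is the hour, firm evidence of the 72-hour condition, and classification of patients with residual cough or a borderline temperature.

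Other limits also stand:

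- Only TTCR is affected in this way. Time to a negative RT-PCR has its own duration field.
- A delay of 36 h cannot be stated as fact, because it presumes a sheet frequency the CRF does not give. A common schedule would delay all arms alike, so the loss shown is mainly one of precision; no bias between arms is demonstrated.
- Item (e) assigns clinical evaluation to a separate investigator, so later reconstruction by treating staff is not a given. That investigator is not described as blinded, however.
- A reader might extend the point to oxygen support and PaO2/FiO2. The support is weak: SpO2 is recorded on room air or oxygen, blood gases are scheduled, the laboratory tables have a row for other results, and the severe form has a ventilation block.

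Some pages are absent from the available copy, so a first-dose time could be recorded on one of them. That would not mend the recovery, cough and temperature items, which are visible on both follow-up forms.

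**Conclusion.** The point holds for TTCR as defined. Both forms lack an onset time and a 72-hour confirmation for recovery, both merge and dichotomise cough, and both omit the temperature site. These three gaps rest only on comparing the protocol's definition with its own form. The missing first-dose time is subject to the pages not shown.

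The size varies by patient:
- Hour-level timing is lost for everyone.
- Recovery status is lost for anyone ticked as still coughing and for any reading above 36.9 and up to 37.2 °C.
- Cough-free patients with clearly normal temperature keep a coarse date, late on average by about 12 h with daily sheets or about 36 h with 72-hourly sheets, under uniform timing of recovery.

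The documents do not give the number of patients in each group. Falling back on the cough box would tighten the cough criterion from mild or absent to absent and so alter the endpoint.

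**What to change.** On both follow-up forms:

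1. Replace the cough tick box with the protocol's own four-level patient-reported scale, and record sputum separately.
2. Add the site of temperature measurement.
3. Add the date and time of first dose, the date and time all four criteria were first met, and the date and time of the 72-hour confirmation.
4. State in the CRF that vital signs and cough grade are entered at least daily.

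The cost is a re-issue of the CRF, a short daily cough question and daily transcription. The cough question should be counted as new work, since nothing in the protocol says the ward already records a grade. No treatment or clinical rule changes. The forms should be corrected before data are collected on them, because cough grade, site and onset time may not be recoverable later.
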